### Eligible participant and exclusion criteria

Patients with resistant hypertension, who are aged between 40 and 70 years, will be recruited from the Lauro Wanderley University Hospital at the Federal University of Paraiba, Brazil, being men or women (women must be postmenopausal, nonmenstruating for at least 1 year and not using hormone replacement therapy), with Body Mass Index ˂40 kg/m^2^ and able to do physical exercise. Patients with resistant hypertension when BP levels are ≥140/90 mmHg for SBP/DBP, respectively, using three or more antihypertensive agents in appropriate doses and combinations, or with controlled BP using four or more antihypertensive agents, will be considered [3] in addition to considering ambulatory BP monitoring (ABPM) records. Controlled BP will be considered for SBP and DBP: at 24 h <130 mmHg and <80 mmHg; awake <135 mmHg and <85 mmHg; and sleeping <120 mmHg and <70 mmHg [40].

After clinical assessment and verifying medical records and biochemical data, patients can be excluded for having a history of ischemic stroke, coronary heart disease, chronic obstructive or restrictive pulmonary disease, peripheral arterial disease, hypo/hypernatremia, hyper/hypothyroidism, chronic atrial fibrillation or a change in drug therapy for an experimental protocol. In the follow-up phase, patients who do not participate in 90% of the exercise training sessions, miss three consecutive training sessions or present any osteoarticular disease that prevents them from continuing the physical training program will be considered as sample loss.

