## Statistical analysis

### Power and sample size

Sample size was calculated using ABPM as the main outcome. Considering the high variance in the results with resistant hypertensive patients [29, 30] and the meta-analysis results of Fagard [28] with hypertensive patients, BP reduction after endurance training of 7 mmHg from SBP and 5 mmHg from DBP was used in the calculation. In order, to provide 80% power to detect a difference of 3 mmHg between the four distinct conditions (exercise intensity and control), a total of 32 patients are indicated to give sufficient power for the study (*n* = 8 for each group). Considering the possible sample loss, 12 patients will be included in each group.

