### Analysis plan

Intragroup and intergroup differences between dependent variables (BP, autonomic modulation, baroreflex sensitivity, blood flow and vascular resistance) considering pre and post interventions (short-term), baseline and post intervention (dependent factor), and exercise intensities or control (independent factor) will be analyzed by two-way analysis of variance (ANOVA) for repeated measures with the Bonferroni post hoc test. Multiple linear regression will be used for analyzing confounding factors (dietary habits and unsupervised physical exercise practice in the follow-up period). Pearson’s correlation test will be used for analyzing the relation between short-term and long-term results. Intention-to-treat will be considered for the patients with an incomplete follow-up period. A *p* value < 0.05 will be considered significant for all evaluations.

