## Discussion

The prevalence of resistant hypertension is about 10% among hypertensive patients. This number is very representative considering the overall prevalence of hypertension and consequent harm to cardiovascular health often associated with morbidity and mortality. Changes in lifestyle are continually recommended, especially in diet adjustment and regular physical exercise.

The guidelines on evaluating BP levels and resistant hypertension pay particular attention to the possibility of misdiagnosis, difficulty of adherence to a newly started treatment, adequacy of combining antihypertensive classes, adequacy of each drug dosage, as well as cases of white coat hypertension. Therefore, resistant hypertension can be real or only apparently spurious [1]. In the present study, the inclusion of each volunteer will consider medical care, medication time without changing for at least 1 year, and the use of ABPM for an appropriate confirmation of resistant hypertension.

There are only a few studies that have investigated physical exercise as an alternative therapy for resistant hypertension treatment, and they have presented promising results [29, 30, 32, 33]. However, these studies did not perform randomization, allocation blindness, appropriate pairing, or detailed description of methods (mainly statistical analysis). Also, the results are also among the main criticisms of the experts [51]. Therefore, the employed study design could hinder correctly interpreting the data, and consequently limit the scientific evidence on clinical utilization of exercise as a tool for hypertensives.

Considering the acute and chronic potential effects of exercise on BP, the lack of responsiveness to antihypertensive drugs can adjust the mechanisms involved in BP control. It is possible that there is also an unexpected response to exercise, since an adverse response to exercise is not uncommon. A considerable percentage of hypertensive or nonhypertensive patients already had an adverse response in previous studies [52–54]. Thus, resistant hypertensive patients can also have difficulty attaining reduced BP.

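### In the 8-week phase, poor attendance or training-limiting joint disease makes a randomised patient "sample loss"; only exercise arms can lose patients this way, and the rule is not reconciled with intention-to-treat

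*Protocol article*

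**What the plan says.** All places are in the protocol article.

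- **Random allocation sequence.** After the four acute sessions, patients are randomised to mild, moderate or high-intensity exercise or control, and followed for 8 weeks.
- **Eligible participant and exclusion criteria, sentence on the follow-up phase.** Three reasons are given. Two concern attendance: "patients who do not participate in 90% of the exercise training sessions, miss three consecutive training sessions". The third is joint disease that makes further training impossible. Any of the three means that the patient "will be considered as sample loss".
- **Aerobic exercise training.** Each exercise group has 24 sessions (8 weeks, three per week). The control group has none.
- **Power and sample size.** 32 patients (8 per group) are said to be enough for 80% power to detect 3 mmHg. Then: "Considering the possible sample loss, 12 patients will be included in each group".
- **Analysis plan.** "Intention-to-treat will be considered for the patients with an incomplete follow-up period".

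The eligibility section also has a separate, earlier list of exclusions, introduced by "After clinical assessment and verifying medical records and biochemical data, patients can be excluded for having a history of ischemic stroke". Its last item is "a change in drug therapy for an experimental protocol".

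**The concern.** The attendance and joint-disease rule acts after allocation, and all three reasons are defined by training. It can therefore mark exercise patients as lost but never a control patient. If marked patients leave the analysis, the 8-week comparison sets selected exercise patients, mostly good attenders, against an unselected control group. That is no longer a comparison of the groups as randomised. Wherever attendance is related to blood pressure change, the estimated effect of exercise is biased.

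The intention-to-treat sentence does not clearly prevent this, because it speaks only of patients with incomplete follow-up. Take a patient who attends 21 of 24 sessions and comes to the 8-week reassessment. Blood pressure data are complete, yet the eligibility section counts this patient as lost. No section says whether the patient is analysed.

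**Working it through.** **1. What the rule demands (inputs from the article).** 0.90 × 24 = 21.6, so 22 sessions are needed: 22/24 = 91.7% passes and 21/24 = 87.5% fails. Any three missed sessions fail, consecutive or not. The consecutive-miss rule adds nobody to the final count, though it can act earlier.

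**2. The plan's own loss allowance.** 4 × 8 = 32 and 4 × 12 = 48, so the totals agree. 8/(1 − 1/3) = 12, so the allowance amounts to one third. No rate or cause is stated, and control is inflated in the same way.

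**3. How many the rule would mark.** Assumption: each session is attended independently with probability p (p is not in the article). Kept fraction = P(X ≥ 22), X ~ Binomial(24, p). For p = 0.90: 0.272 + 0.213 + 0.080 = 0.564.

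| p | kept | marked as lost | expected kept of 12 |
|---|---|---|---|
| 0.85 | 28% | 72% | 3.4 |
| 0.90 | 56% | 44% | 6.8 |
| 0.95 | 88% | 12% | 10.6 |
| 0.97 | 97% | 3% | 11.6 |

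Control loses none by this rule. At p = 0.90 the expected number kept is already below the 8 that the plan requires.

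**4. Possible bias.** Assumptions: no true effect; SD of change 8 mmHg; adherence and blood pressure fall jointly normal with correlation r; the least adherent are removed. With kept fraction k and z = Φ⁻¹(1 − k), the shift in the exercise mean is r × SD × φ(z)/k, in the direction of a larger fall.

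| k | φ(z)/k | r = 0.2 | r = 0.4 |
|---|---|---|---|
| 0.667 (the plan's allowance) | 0.3636/0.667 = 0.545 | 0.87 mmHg | 1.75 mmHg |
| 0.564 (p = 0.90) | 0.3938/0.564 = 0.698 | 1.12 mmHg | 2.23 mmHg |
| 0.884 (p = 0.95) | 0.1952/0.884 = 0.221 | 0.35 mmHg | 0.71 mmHg |

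The first two rows give about 0.9 to 2.2 mmHg, that is 0.87/3 = 29% to 2.23/3 = 74% of the 3 mmHg target. The shift is proportional to the SD. The article states no SD. The one that makes 8 per group give 80% power for 3 mmHg in a two-sided t test is 1.99 mmHg; with it the same two rows run from 0.545 × 0.2 × 1.99 = 0.22 to 0.698 × 0.4 × 1.99 = 0.56 mmHg.

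A simpler illustration: if the 4 of 12 removed respond 3 to 5 mmHg worse than the 8 kept, the arm mean shifts by 3 × 4/12 = 1.0 to 5 × 4/12 = 1.7 mmHg.

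**5. The price of keeping everyone.** At that back-solved SD of 1.99 mmHg, power for 3 mmHg is 80% at 8 v 8, 88% at 12 control v 8 exercise, and 94% at 12 v 12. If 4 of 12 are kept and get half the effect, the mean effect is 3 × (8 + 2)/12 = 2.5 mmHg and power is 84%. If they get none, it is 3 × 8/12 = 2.0 mmHg and 65%.

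**The case against.** **The sections may fit together.** Being counted as sample loss is not the same as being excluded from analysis. The eligibility section might define who counts as lost, and the analysis plan might then bring these patients back by intention-to-treat. This stands in part: removal is an inference, and the text is unreconciled rather than flatly contradictory. But the sample size section uses the same term for patients who will not contribute to the required 8, and the intention-to-treat sentence does not clearly cover a poor attender with complete data.

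**The size is assumed.** This stands. Session attendance, the SD of 8 mmHg and the correlation are not in the article. That the bias favours exercise requires that better attenders also show larger falls. The one-sided filter itself needs no such assumption.

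**Stronger readings that a reader might infer, but that the article does not support:**

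- *Any patient whose drugs change is dropped after randomisation.* That item is in the general exclusion list, which is permissive and follows clinical assessment; it is not among the follow-up reasons. The Discussion treats drug stability as an inclusion matter ("medication time without changing for at least 1 year"). A drug change could also occur in any arm. Only its timing is unclear.
- *The extra third is budgeted for poor attendance.* No cause is given, and control, which cannot fail on attendance, is inflated equally.
- *Repeated-measures ANOVA makes intention-to-treat impossible.* A poor attender may have a post-training value, and missing values can be imputed. Such handling may properly be left to the full protocol or SAP.
- *The whole randomised comparison is lost.* The rule is confined to the follow-up phase; the acute crossover sessions, also part of the primary outcome, are untouched.

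**Conclusion.** The point holds for the 8-week phase. A rule acting after randomisation, which only exercise patients can meet, marks patients as lost, and the article does not say that they stay in the analysis. This needs correcting before the 8-week results are analysed, because following the rule as written would filter one side of the comparison with control on the primary outcome.

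The threshold of 22 of 24 sessions is exact. The share removed, about 44% or 12% of exercise patients, rests on independent sessions at 90% or 95% attendance. The bias of about 0.9 to 2.2 mmHg rests on an SD of 8 mmHg, a correlation of 0.2 to 0.4 and removal of one third to 44%; it is smaller with a smaller SD or better attendance, and absent if adherence is unrelated to blood pressure change.

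**What to change.** 1. In the eligibility section, state that sample loss for attendance, consecutive misses or osteoarticular disease does not remove a patient from the analysis.
2. Take the planned 8-week blood pressure reassessment in every randomised patient, whatever the attendance.
3. Make the primary 8-week analysis all randomised patients as allocated, with a method that keeps incomplete cases, for example a likelihood-based mixed model.
4. Record attendance, and report the attendance-based set only as a per-protocol sensitivity analysis.
5. Reconcile the eligibility, sample size and analysis plan sections, so that the term has one meaning.
6. For the drug-change item, say only whether it applies before or after allocation. If after, keep those patients in the as-allocated analysis.

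The cost is wording, plus making sure that poor attenders return for a visit that is already planned. The downside is an estimate diluted by non-adherence, with some loss of power: at the back-solved SD, 84% or 65% instead of 94% if a third of an exercise arm gets half or none of the effect. The sample size section should therefore say whether 3 mmHg refers to the as-allocated effect.

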### Random allocation sequence

Randomization will be done using a sealed opaque envelope. All the patients will be submitted to perform four short-term interventions (within design): mild aerobic exercise, moderate aerobic exercise and high-intensity aerobic exercise and a control session, in random order and on separate days. After the short-term sessions, all the patients will be randomly allocated into four groups and followed up for 8 weeks (between design): mild aerobic exercise group, moderate aerobic exercise group, high-intensity aerobic exercise group and the control group.

### Acute exercise interventions

Considering the recommendations of the American College of Sports Medicine [41] and adjusting tolerance estimated by untrained resistant hypertensive patients, each aerobic exercise session will be 40 min long (warm-up: 5 min; intervention: 30 min; and cool-down: 5 min). The control session also will last 40 min, but with rest in a seated position.

The cardiopulmonary exercise test will be used to determine the maximal aerobic capacity at peak exercise (VO_2_peak), anaerobic threshold and the respiratory compensation point. The heart rate corresponding to the anaerobic threshold and the respiratory compensation point will be used for the prescription of the mild-, moderate- and high-intensity protocols:Mild aerobic exercise: continuous 30-min intervention 10% below the anaerobic threshold to the anaerobic threshold pointModerate aerobic exercise: continuous 30-min intervention at the anaerobic threshold point to the respiratory compensation pointHigh-intensity aerobic exercise: interval of 30-min intervention: 10 stimuli of 1 min above the respiratory compensation point with 2 min interval of passive rest after each stimulusControl: 40 min of rest in a seated position

### Aerobic exercise training

After short-term interventions, the patients will be randomly allocated into four groups for 8 weeks, training three times per week. It will be recommended to the patients to continue with their same daily activities and food. The chronic interventions will be in the same format as the acute interventions:Mild aerobic exercise group: 24 sessions of continuous 30-min intervention 10% below the anaerobic threshold to the anaerobic threshold pointModerate aerobic exercise group: 24 sessions of continuous 30-min intervention at the anaerobic threshold point to the respiratory compensation pointHigh-intensity aerobic exercise group: 24 sessions of 30-min interval intervention: 10 stimuli of 1 min above the respiratory compensation point with 2-min interval of passive rest after each stimulusControl group: without aerobic exercise training. Patients will be instructed to not initiate any supervised physical exercise program until the end of the reevaluations

All patients will be frequently informed about the research progress and its partial results throughout the follow-up period. In addition, the researchers will maintain constant contact with the physicians responsible for each patient. The physicians and patients will receive a final report with the results at the end of study.

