## Methods/design

This is a randomized controlled clinical trial with single-blind data analysis. The Standard Protocol Items: Recommendations for Interventional Trials (SPIRIT) flow chart and enrollment schedule, interventions and assessments for the trial are given in Fig. 1 and the SPIRIT Checklist in Additional file 1. Figure 2 presents the experimental research design stages. In addition to ongoing medical monitoring, all individuals will be assessed by anamnesis, anthropometric measurements, biochemical tests, echocardiogram, cardiopulmonary exercise test, information about lifestyle (including dietary habits), and habits/history of physical activity before each short-term intervention and after the follow-up period.

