### Measurements

Individuals will receive the following instructions 24 h prior to measuring their biological signals: maintain their normal drug-use routine and sleep and meal hours; do not drink alcohol, tea, coffee, soda, or any food/drink containing caffeine. In addition, on the experiment day they will be asked to ingest a light meal 2 h before initiating the protocol. Patients will be asked to record their activities 24 h following the experiment, such as working hours, sleep schedule, meals, use of medication and any complications that they consider important (e.g., stressful situations). The same instructions will be given in the revaluation after the follow-up period.

In each short-term experimental session and follow-up phase, the biological BP signal, electrocardiogram (ECG) and blood flow will be continuously measured using 500-Hz frequency per channel in WINDAQ software (DATAQ Instruments DI-720 Acquisition, Akron, OH, USA). BP will be recorded by ABPM (Dynamapa Cardios®, São Paulo, Brazil) measured in the nondominant arm by a Dixtal® oscillometric semiautomatic monitor (Dixtal®, DX 2020, Manaus, Brazil) and by Finometer oscillometric equipment (Ohmeda 2300 Monitoring Systems, Englewood, CO, USA). BP values will be obtained immediately before exercise, 30 and 60 min after each intervention (ABPM, Dixtal® and Finometer methods), and 24 h (ABPM) after the end of the intervention. ECG will be evaluated in the DII derivation (right and left arm). Forearm blood flow will be collected by venous occlusion plethysmography [42] apud [43] (Hokanson®/EC6 plethysmograph, Bellevue, WA, USA). During blood flow signal collection, BP values will be registered by Dixtal® oscillometric semiautomatic monitor (Dixtal®, DX 2020, Manaus, Brazil). All the measurement methods will be repeated in an experimental session without any intervention after the follow-up period in the same sequence and procedure.

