## Outcomes

### Primary outcome

#### Blood pressure

For the BP measurement in the office, analysis will consider the difference between post-intervention and pre-intervention values. For ambulatory analysis, BP will be considered as sleep and awake periods, and the difference between 24-h post-intervention and pre-intervention values. In the follow-up analysis, baseline BP values (considering control session values without intervention) and post-training BP values will be evaluated.

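### Patients are to be told the study's partial results during the 8-week follow-up, before the long-term blood pressure outcome is measured

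*Protocol article*

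**What the plan says.** The last paragraph of Aerobic exercise training makes three separate commitments for the follow-up phase:

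- To patients, during follow-up: "All patients will be frequently informed about the research progress and its partial results throughout the follow-up period".
- To treating physicians, during follow-up: "the researchers will maintain constant contact with the physicians responsible for each patient". Results are not mentioned here.
- To both, at the end: "The physicians and patients will receive a final report with the results at the end of study".

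Methods/design describes the study as a "randomized controlled clinical trial with single-blind data analysis". Random allocation sequence says that "all the patients will be randomly allocated into four groups and followed up for 8 weeks (between design"). Under Measurements, "All the measurement methods will be repeated in an experimental session without any intervention after the follow-up period in the same sequence and procedure". The primary outcome section adds that for follow-up, "baseline BP values (considering control session values without intervention) and post-training BP values will be evaluated".

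Two further provisions bear on the point. Aerobic exercise training advises patients to keep their usual activities and diet, and tells controls not to begin a supervised exercise programme before reassessment. The Analysis plan names diet and unsupervised exercise during follow-up as confounders to be handled by multiple linear regression.

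**The concern.** The partial results reach patients between randomisation and the measurement of the long-term primary outcome. Patients in an exercise trial cannot be blinded to their group, which makes control of the information they receive during follow-up more important.

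Two effects are possible, and they pull in opposite directions:

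- **Control group.** A patient told that exercise appears to lower BP has a reason to start exercising. Only supervised programmes are ruled out. This lowers BP in controls and shrinks the difference the trial is meant to detect.
- **Training groups.** Encouraging results can raise expectation or prompt other changes, for example in diet. This can enlarge the difference for reasons other than the assigned exercise intensity.

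The net direction is therefore unknown in advance. The concern is confined to the 8-week phase. Each patient's short-term sessions are finished before follow-up begins.

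**Working it through.** **Order of events.** From the sections cited above, the sequence for each patient is: short-term sessions; random allocation to one of four groups; 8 weeks of follow-up with partial results shared throughout; BP reassessment; final report. The final report is promised separately, so the partial results are an additional and earlier release.

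**Existing safeguards.**

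| Safeguard | Where | What it leaves open |
|---|---|---|
| Blinded data analysis | Methods/design | Does not affect what patients know or do |
| Advice to keep usual activities and diet | Aerobic exercise training | A recommendation only |
| Controls not to start a supervised programme | Aerobic exercise training | Unsupervised exercise is not covered |
| Regression on diet and unsupervised exercise | Analysis plan | Both arise after randomisation and may themselves be consequences of group or of the shared results, so adjustment cannot be relied on to restore the randomised comparison |

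**Size, as an illustration.** The document gives no rate at which patients would react, so the share is assumed.

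Inputs:

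- Share of controls who respond, p: 1/8 or 1/4 (assumed). With the planned 12 per group, 1/4 is 3 patients.
- Fall in systolic BP in a responding control, e: 3.3 mmHg (the meta-analysis of normotensive and hypertensive patients cited in Background) or 7 mmHg (the training reduction used in Power and sample size).
- Target difference: 3 mmHg (Power and sample size).

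Formula: shift in control mean = p × e. Share of target = p × e / 3.

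| p | e (mmHg) | Shift (mmHg) | Share of 3 mmHg |
|---|---|---|---|
| 1/8 | 3.3 | 0.125 × 3.3 = 0.41 | 14% |
| 1/8 | 7 | 0.125 × 7 = 0.875 | 29% |
| 1/4 | 3.3 | 0.25 × 3.3 = 0.83 | 28% |
| 1/4 | 7 | 0.25 × 7 = 1.75 | 58% |

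A true difference of 3 mmHg between a training group and control would then appear as 3 − 0.41 = 2.59 mmHg at the mild end and 3 − 1.75 = 1.25 mmHg at the severe end. The 7 mmHg rows are an upper end: someone who starts exercising alone partway through 8 weeks is unlikely to gain the full effect of a training programme. The article states no standard deviation, so these shifts cannot be turned into a loss of power without a further assumption. The effect in the training groups has no figure in the document and is not quantified.

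**The case against.** The strongest reply has four parts.

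- **The partial results may be harmless.** The text does not say that they are split by group. Each patient has already completed four short-term sessions, so a patient's own readings could be reported without comparing the parallel groups. This stands as far as it goes. A reader might infer that producing partial results requires comparing groups while the trial runs and so undermines the blinded analysis; the document does not support that. However, the sentence refers to results of the research, and nothing limits it to a patient's own readings.
- **Physicians are not named as recipients.** A reader might infer that physicians will see partial results and change drug treatment by group. The text promises them contact during the study and results only in the final report. The contact may equally serve medical monitoring or keeping therapy stable. This objection stands.
- **Contamination was foreseen.** The advice on usual activities and the planned regression show that the authors considered it. Both reduce the concern without removing it, for the reasons given in the table of safeguards.
- **The added effect is speculative.** Patients know their group and have tried every intensity, so some motivation to exercise exists anyway. This is fair, and the document does not allow the sentence's own contribution to be separated out. But this part of the risk is avoidable, whereas the open-label design is not.

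It could also be said that a condensed article leaves patient communication to the full protocol. Here, though, the article states a positive rule to release results, so the point does not rest on an omission.

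**Conclusion.** The point holds for the 8-week phase. The plan commits to giving patients partial results before the long-term primary BP outcome is measured, in a trial where blinding is claimed only for the data analysis, and the stated safeguards do not fully contain the effect. The likely routes are unsupervised exercise among controls, which dilutes the contrast, and changed expectation or behaviour in the training groups, which may inflate it.

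The size is not derivable from the document. With one control in eight to one in four responding by 3.3 to 7 mmHg, the control mean shifts by about 0.4 to 1.75 mmHg, or 14% to 58% of the 3 mmHg target. The shares are assumptions, and the upper BP figure is generous.

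The conclusion does not depend on the partial results being comparative or on physicians receiving them, and neither is claimed. The change is one the sponsor should make. Trial status says recruitment is continuing, so it can still protect patients who have yet to be reassessed.

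**What to change.** Replace the sentence on partial results with a rule to this effect: patients and training staff may be told how the study is progressing, but no group-level or between-arm outcome results are released to patients, training staff or treating physicians until all 8-week reassessments are complete and the database is locked.

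State in the same place that individual clinical and safety information and contact with treating physicians are unaffected, so that the rule does not touch patient care. The final report to physicians and patients remains as planned.

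The cost is one sentence in the protocol, with a small downside: patients wait until the end of the study for results. Motivation to exercise that comes from a patient's own experience of the short-term sessions would remain. It belongs to the design, and the rule does not try to remove it.
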